**Opportunity:**
▪ **Physical opportunity:** Access to medical resources in the family’s area, convenience of prenatal diagnosis services, and reasonable diagnostic costs all impact a woman’s opportunity to participate in diagnosis. The intervention will ensure that families have easy access to diagnostic appointments and information. Additionally, providing family-based diagnostic education will help reduce fear and uncertainty about prenatal diagnosis, boosting confidence in participating.▪ **Social opportunity:** Family health theory emphasizes the importance of family support systems. The attitudes and support of family members (particularly husbands, parents, or in-laws) are crucial for a pregnant woman’s decision to undergo prenatal diagnosis. If family members lack knowledge or awareness of the importance of diagnosis, it may affect the woman’s decision. Therefore, the intervention will strengthen communication and interaction among family members, providing knowledge dissemination at the family level. By strengthening the role of family members and providing emotional support, anxiety and depression can be reduced.
**Motivation:**
▪ **Reflective motivation:** The attitude and awareness of the target family regarding prenatal diagnosis directly affect behavior. Pregnant women and their families may feel anxious about the diagnosis results, fearing the detection of genetic diseases or abnormal outcomes. Family-level health education will help reduce misunderstandings and anxiety, enhancing the understanding of the necessity and benefits of prenatal diagnosis.▪ **Automatic motivation:** Habits, emotions, and family culture can have a significant impact on behavior. Some families may have doubts or resistance towards medical diagnosis. By leveraging emotional support, emotional encouragement, and sharing successful case studies, families can be effectively motivated to actively participate in the diagnosis process.

**Step 2: Choosing intervention functions and strategies (BCT) (integrating family health factors)**

Based on the integration of the COM-B model and Family Health Theory, the following intervention strategies will help overcome behavioral barriers and focus on emotional management, ultimately increasing prenatal diagnosis rates and improving pregnancy outcomes:

Education:Purpose: Improve the understanding of prenatal diagnosis for pregnant women and their family members, and provide psychological health education to help them understand the sources of anxiety and depression and how to cope.Intervention Strategies:▪ Health education: Design family health education materials for high-risk pregnant women and their partners, providing information on prenatal diagnosis, diagnostic procedures, and interpreting results (e.g., via WeChat messages, video courses). Design and push psychological health education materials to help identify early signs of anxiety and depression and offer emotional regulation techniques.▪ Online expert courses: Online Expert Courses will be delivered via WeChat platform. Invite genetic experts to hold online lectures for families, answering questions related to the diagnosis process and boosting confidence in prenatal diagnosis.Persuasion:Purpose: Use emotional encouragement and positive feedback to reduce anxiety and worry, and increase positive attitudes towards prenatal diagnosis.Intervention Strategies:▪ Emotional encouragement: Share case stories related to family health, emphasizing the importance of prenatal diagnosis for family health. By showing successful diagnosis experiences of real families, families will view diagnosis as an act of caring for their loved ones, eliminating the fear of diagnosis results.▪ Role models: Invite families who have completed prenatal diagnosis to share their experiences and encourage partners and family members to talk about the support they provided during the diagnosis process. This can influence other families to form positive health behaviors and increase trust in prenatal diagnosis, reducing anxiety about negative results.
**Incentivisation**:Purpose: Encourage families to actively participate in prenatal diagnosis through a reward system while alleviating the negative impact of emotional barriers on decision-making.Intervention strategies:▪ Family Reward System: Set up a family health reward program to encourage both partners to participate in prenatal diagnosis. Families who complete the diagnosis will be rewarded or recognized with a “Healthy Family” title, acknowledging their active participation in health decision-making.▪ Group incentives: Organize health knowledge competitions, family check-in activities, and emotional regulation challenges in WeChat groups to encourage family members to participate and share their diagnostic process, strengthening collective involvement and family cohesion.
**Training**:Purpose: Enhance the self-management abilities of pregnant women and their family members during the prenatal diagnosis process and provide emotional management tools.Intervention strategies:▪ Appointment and results interpretation training: Create a detailed prenatal diagnosis appointment guide and provide hands-on training for family members to ensure they can complete the diagnostic process smoothly. Provide online courses on interpreting diagnostic results, helping families understand the meaning of results and subsequent measures.▪ Emotional management training: Organize emotional management training to teach how to cope with prenatal anxiety and depression, helping pregnant women adjust their mindset.
**Environmental restructuring:**
Purpose: Create a supportive social environment for the target families, increasing their access to diagnostic services and knowledge, as well as emotional support.Intervention strategies:▪ Online family support community: Establish a family health support platform through WeChat groups, encouraging family members to share experiences, discuss diagnostic-related issues, and provide online Q&A with doctors. This promotes mutual support within families and communities, reduces feelings of isolation, and enhances emotional support.▪ Optimizing family-friendly diagnostic services: Provide convenient diagnostic appointment services, design diagnostic reminders, and support functions (e.g., pre- and post-consultation calls).
**Modeling:**
Purpose: Encourage target families to model healthy behaviors through examples.Intervention strategies:▪ Model Families’ Experience Sharing: Push stories of families who have completed prenatal diagnosis and overcame anxiety with emotional support. Show how they successfully managed their emotions and actively participated in the diagnosis process. Real-life case examples will motivate other families to get involved and reduce their fears and anxieties about the process.▪ Family demonstration: Encourage families, especially husbands, who have completed the prenatal diagnosis to share how they provided emotional support during the diagnosis process and helped pregnant women overcome emotional barriers. These model families’ experiences will serve as learning examples for other families.
**Enablement:**
Purpose: Help the target families overcome behavioral barriers and take action immediately by providing personalized support and real-time reminders, especially to help pregnant women and family members manage emotions and participate in prenatal diagnosis.Intervention strategies:▪ Personalized reminders: Send customized reminders in the WeChat group for each family, reminding them of the prenatal diagnosis appointment and important details. Also, remind pregnant women and their family members to focus on emotional regulation. For example: "Dear XX family, your prenatal diagnosis appointment is coming up, please make sure you're ready and maintain a positive attitude!"▪ Emotional support and psychological counseling: Provide psychological counseling for women and family members who are worried about the diagnosis results or feel anxious about the process. This will help them overcome emotional barriers and complete the prenatal diagnosis with peace of mind.

**Step 3: Phase-wise implementation and evaluation**

**implementation in phases:**

The intervention will be implemented in three phases, with each phase involving specific tasks, staff responsibilities, and procedures to ensure smooth execution.

**Phase 1: Dissemination of information and emotional support (Week 1-4)**

**Responsible personnel**: A team consisting of 3 trained nurses, 2 psychologists, and 1 genetic expert will handle the educational and emotional support activities.
**Competencies**: Nurses will be trained in prenatal care and communication skills, psychologists will specialize in emotional support and anxiety management during pregnancy, and the genetic expert will have expertise in prenatal diagnostics and genetic counseling.
**Process**: The team will use WeChat groups and official WeChat accounts to deliver educational content on prenatal diagnosis, covering topics such as its importance, process, and potential outcomes. Psychological support will also be provided to help reduce anxiety and fear among pregnant women. Each session will last approximately 30 minutes, with weekly check-ins to track progress. Additionally, the genetic expert will host online lectures for families, answering questions related to the diagnostic process and boosting confidence in prenatal diagnosis. Success stories from previous participants will also be shared in the early educational materials to further enhance participants’ confidence.
**Incident management**: If a participant shows severe anxiety or depressive symptoms beyond normal concerns, a psychologist will be assigned for an in-depth individual consultation to provide additional emotional support.

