### Design

2.1

This study is a single-blind, interventional randomized controlled trial conducted at the Inner Mongolia Maternity and Child Health Care Hospital. The aim is to evaluate the impact of a mobile health intervention based on the Behavior Change Wheel theory and Family Health Theory on the prenatal diagnosis rate and pregnancy outcomes of high-risk pregnant women undergoing prenatal screening. The study will be conducted from June 2025 to June 2026. The flowchart of the study is shown in **Figure 3** and **4**.

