**Inclusion Criteria**

Aged 18 years or older.High-risk pregnancy as determined by prenatal screening results.Basic ability to use mobile devices and WeChat.Willingness to participate and sign an informed consent form.

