### Sample size estimation

2.3

This study is a randomized controlled trial, where the intervention group will receive the mobile health intervention and the standard care group will receive standard care. The outcome measure is the prenatal diagnosis demand. Based on previous randomized controlled trials related to willingness to undergo screening for related diseases, the intervention group’s demand proportion is 53.4%, and the standard care group’s is 34%, showing an increase of approximately 19.4% (28). We predict that the mobile health intervention based on the Behavior Change Wheel theory and Family Health Theory may lead to a doubling of the demand proportion (38.8%), reaching 72.8% (29). The expected demand proportion for the intervention group is 72.8%, and for the standard care group is 34%. Using a two-sided test with α = 0.05, β = 0.2, and power (1-β) = 80%, the sample size ratio between the two groups is 1:1. After using the PASS software (version 2021) to calculate the relevant values, it was determined that 23 participants per group would be required. Considering a 20% dropout rate, the final sample size for each group is 29 participants, for a total of 58 participants.

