#### Standard care group

2.6.2

The standard care group will receive routine prenatal care without the additional mobile health intervention. Routine care includes basic information provided by medical staff at regular checkups, such as prenatal vitamins, ultrasound scans, and general prenatal education.

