#### Screening of health education materials

2.7.2

After the collection and organization of the health education materials, a thorough screening process will be conducted. A panel of experts specializing in the field of birth defects will be responsible for reviewing the content of all materials. These experts, with deep knowledge in prenatal care, genetic counseling, and related areas, will evaluate the materials for scientific accuracy, clarity, and their ability to effectively communicate essential information to patients and the general public.

The experts will suggest any necessary modifications to improve the materials, ensuring they are scientifically sound and easily understood by a wide range of audiences. Any materials that do not meet the established criteria will be excluded from the final selection. The remaining high-quality materials will then be categorized into relevant areas such as awareness of birth defects, prevention strategies, prenatal care, and genetic counseling, among others. This classification will allow for the creation of targeted, informative push recommendations tailored to the specific needs of patients and the public.

The final selection of health education materials will be compiled into a comprehensive database, which will serve as a central resource for the study. This database will include key details for each material, such as the title, relevant links, sources, and material types (e.g., articles, videos, infographics). This resource will also be used to generate personalized push notifications to patients, offering them the most relevant and up-to-date educational materials. By ensuring that only high-quality, evidence-based resources are included, this process will support effective health education and help patients make informed decisions regarding birth defect prevention and care.

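### Study content is assigned to official WeChat accounts and to pushes not limited by arm, so control women in the same hospital could be exposed and the contrast diluted

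*Protocol article*

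**What the plan says.** The protocol article describes one hospital with individual randomisation (sections 2.1 and 2.4): "This study is a single-blind, interventional randomized controlled trial conducted at the Inner Mongolia Maternity and Child Health Care Hospital". Every participant, in either arm, must meet the inclusion criterion "Basic ability to use mobile devices and WeChat" (section 2.2).

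The control condition is set in section 2.6.2: "The standard care group will receive routine prenatal care without the additional mobile health intervention".

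Two places describe how study content is sent out:

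- Section 2.6.1, Phase 1 (Week 1-4): "The team will use WeChat groups and official WeChat accounts to deliver educational content on prenatal diagnosis". Official accounts are named as a channel alongside the groups.
- Section 2.7.2, on the screened materials: classification will support "targeted, informative push recommendations tailored to the specific needs of patients and the public", and of the resulting database it says "This resource will also be used to generate personalized push notifications to patients". Neither sentence names an arm.

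Section 2.8.1 counts a woman as having demand if she answers yes to any one of three items: willingness, a plan within six months, or diagnosis already done. Table 1 schedules demand and knowledge at Month 0, Month 3 and after delivery.

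**The concern.** Taken at face value, the audience in section 2.7.2 includes control women, since they are patients of this hospital and can use WeChat. Section 2.6.2 intends that they receive none of the mobile intervention. Nothing in the two delivery passages keeps the content on one side of the randomisation.

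The primary endpoint is sensitive to this. A single yes to willingness is enough, and educational material alone could move that answer without counselling, reminders or incentives. The knowledge outcome is a direct target of the same material. Leakage would therefore raise the control results and pull the difference towards zero. The sample size in section 2.3 makes no allowance for it. If the trial then found no difference, it would have no direct record of control exposure to help interpret that result.

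**Working it through.** **Inputs from section 2.3.** Expected demand is 72.8% (intervention) and 34% (control), a difference of 38.8 points. The test is two-sided at α = 0.05 with 80% power and 1:1 allocation. The stated size is 23 per group, or 29 after 20% dropout.

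**Input not in the article.** The share of controls exposed, c, is not given. It is assumed here over 0% to 30%.

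**Step 1: reproduce the plan's figure.** Two proportions, unpooled variance:

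n = [p1(1−p1) + p2(1−p2)] × (1.960 + 0.842)² / (p1−p2)²

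- p1(1−p1) = 0.728 × 0.272 = 0.1980
- p2(1−p2) = 0.34 × 0.66 = 0.2244
- n = 0.4224 × 7.849 / 0.1505 = 22.02, rounded up to 23
- 23 / 0.80 = 28.75, rounded up to 29

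The stated 23, 29 and 58 reproduce. The pooled-variance formula gives 25, so the unpooled form is used below.

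**Step 2: dilution model (assumption).** A share c of controls responds at the intervention rate:

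control rate = 0.34 + c × 0.388

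**Step 3: power at 23 evaluable per arm.** Power = Φ(d / √(v/23) − 1.960), where d is the diluted difference and v is the sum of the two binomial variances.

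| Controls exposed, full effect | Control rate | Difference | Power (unpooled) | Power (pooled) |
|---|---|---|---|---|
| 0% | 34.0% | 38.8 points | 81.7% | 76.9% |
| 10% | 37.9% | 34.9 points | 72.0% | 67.4% |
| 20% | 41.8% | 31.0 points | 61.1% | 57.0% |
| 30% | 45.6% | 27.2 points | 49.6% | 46.4% |

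Worked line for 10%: v = 0.1980 + 0.3788 × 0.6212 = 0.4333; √(0.4333/23) = 0.1373; 0.3492/0.1373 = 2.544; 2.544 − 1.960 = 0.584; Φ(0.584) = 0.720.

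The pooled column is a sensitivity check. It starts below 80% because of the formula, not because of contamination, so it should not be read as extra loss.

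**Step 4: partial effect.** If exposed controls gain half the effect, 20% exposure gives 0.34 + 0.20 × 0.5 × 0.388 = 0.3788. That is the 10% row: 72.0%.

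**Step 5: size needed to restore 80% power** (unpooled, same model). At 10% exposure, 28 per arm, or 35 after dropout. At 20%, 36 per arm, or 45 after dropout. The article plans 29.

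**The case against.** The strongest reply is that no sentence says control women can follow the accounts or will be sent a push. Phase 1 sits under the intervention-group heading, so it describes delivery to that arm. Section 2.7.2 concerns screening and classifying materials, and its mention of the public can be read as the readership for which content is tailored. Section 2.6.2 sets the rule for controls. A reader might infer that the article contradicts itself, or that controls will certainly be exposed. The text supports neither: the sections can be read consistently, and what they leave is an ambiguity and a risk.

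Further points on that side:

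- Account permissions and exposure monitoring may be in the full protocol. The absence of an exposure item from Table 1 is therefore not an error in itself. The criticism rests on the channels and audience that the article does name.
- Only education could leak by this route. Family reminders, counselling, appointment help, incentives and group activities are described for intervention families. Giving exposed controls the full effect is therefore an upper bound.
- Section 2.7.1 draws on sources that are already public, so some background exposure will occur whatever is done.
- Knowledge is measured in both arms over time. A rise among controls would be an indirect signal, so it goes too far to say that contamination would be undetectable.
- Asking controls about study materials by name would sit badly with the participant blinding claimed in section 2.4.

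All of this stands, and it limits the claim. It does not remove it: a channel beyond the groups and an audience not limited by arm are stated, and closing the route is cheap.

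**Conclusion.** The point holds as a risk of dilution. The named channels and audience could carry educational content to control women, and any effect of that leakage would be towards no difference in demand and knowledge. The sample size of 23, 29 and 58 is arithmetically sound but has little margin. On the plan's own rates, power at 23 per arm falls from 81.7% to 72.0% at 10% exposure and to 61.1% at 20%. These losses rest on an assumed exposed share and on exposed controls gaining the full effect, so they show scale and are not forecasts. With no dropout (29 per arm), power at 20% full-effect exposure would be 71.1%. The change is worth making before recruitment if possible; the evidence does not show that contamination will occur.

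**What to change.** State in section 2.6.1 (Step 3) and section 2.7.2 that all study content, lectures and pushes go only to closed, invitation-only WeChat groups of intervention-arm families. State that nothing from the study database will appear on an official account, or be pushed to other patients or the public, until the last participant's after-delivery assessment. Month 3 is too early an end, because demand, knowledge and pregnancy outcomes are collected again after delivery.

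Add to Table 1 one neutrally worded item for both arms, at Month 3 and after delivery: whether the woman received material about prenatal diagnosis through WeChat, and from what source. It should not mention the study's materials, so that it does not work against the blinding. Report the share of controls exposed alongside the primary result.

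The cost is protocol wording, a channel setting, one extra questionnaire item and later public release of the materials. Exposure to material that is already public is not removed, but the item would help to describe it.

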**Phase 2: Appointment scheduling and family support (Week 5-8)**

**Responsible personnel**: A team consisting of 2 nurses, 1 social worker, 1 psychologist, and 1 genetic expert.
**Competencies**: The nurses will guide participants in scheduling their prenatal diagnosis appointments, the social worker will facilitate family communication and ensure family members understand their supportive roles, the psychologist will provide emotional support and counseling to help manage anxiety and emotional concerns, and the genetic expert will provide specialized input on prenatal diagnosis and genetic counseling.
**Process**: During this phase, the nurses will assist pregnant women and their families in scheduling prenatal diagnosis appointments and provide support to ensure they understand the entire process. The social worker will educate family members on how to emotionally and physically support the pregnant woman. The genetic expert will host online lectures for the families to answer questions about the diagnostic process and boost their confidence in prenatal diagnosis. Each session will last 45 minutes and will be scheduled bi-weekly. The social worker will also send customized reminders to each family in the WeChat group, reminding them of the upcoming prenatal diagnosis appointment and key details while encouraging emotional regulation, such as, “Dear XX family, your prenatal diagnosis appointment is approaching, please be prepared and maintain a positive mindset!” For those who are anxious about the results or the process, the psychologist will provide counseling to help them manage their emotional concerns and complete the prenatal diagnosis with peace of mind.
**Incident management**: If a participant experiences logistical issues, such as scheduling conflicts or transportation problems, the social worker will step in to provide solutions or connect the participant with local resources to resolve these issues.

